### Randomization and Blinding

#### Overview

After preassessments, participants will be allocated to either of 2 intervention groups to eliminate selection bias and control for any extraneous variables: EMT+PE or the usual-care intervention. Block randomized trials will be conducted for each age group using the blockrand package in R software (version 4.1.3; The R Foundation). Randomization will be based on age (3 age groups) and the 2 interventions. The flow of participants through the study is illustrated using the CONSORT (Consolidated Standards of Reporting Trials) flowchart in Figure 1.

#### Blinding of Raters and Reliability of the Data

Trained and experienced raters who are blinded to the grouping of participants will transcribe audio and video samples of speech and language. The samples will be collected from the parents at home as they are interacting with their children using toys and pictures, using the Profiles of Early Expressive Phonological Skills (PEEPS) assessment.

### Intervention

#### EMT+PE Intervention

The EMT+PE intervention consists of implementing supportive speech and language strategies by parents in their interaction with their children. All parents will be trained in accordance with the Teach-Model-Coach-Review (TMCR) instructional model that has been adapted for the telepractice environment [9,30]. The Teach component of the instructional approach involves introducing targeted supportive strategies. The Model component includes the implementation of strategies by a clinician when interacting with a child—we will implement this component by showing recorded video examples of strategies. The Coaching aspect entails parents using strategies during their interaction with their children. The Review component includes monitoring and evaluating the entire session and planning for the next session at the end of every session. EMT+PE treatment principles for the intervention group are illustrated in Figure 2.

**Figure 2 figure2:**
[figure not shown]
Principles of the EMT+PE (Enhanced Milieu Teaching with Phonological Emphasis) intervention. EMT: Enhanced Milieu Teaching.

#### Speech Target Selection

Speech targets for each child are determined by analyzing the errors produced in their speech sounds during the PEEPS assessment. A list of sample words will be created from the speech sound errors observed in the children’s PEEPS assessment. To select the target speech sounds, developmental norms and the frequency of speech sound errors related to cleft palate, including high-pressure and fricative consonants in words with the syllabic consonant-vowel-consonant-vowel structure, are taken into account. For each child, place, and manner of articulation, pre- and postvocalic voicing are considered. Once a participant can produce 7-10 words per minute, a speech recast strategy is integrated into the intervention process.

#### Usual-Care Intervention

Children assigned to the usual-care intervention (control) group will be assessed twice before and after the 3-month intervention. If they are not, they will be enrolled in cleft teams. They will receive speech and language therapy there in accordance with a specific protocol. Regular evaluations administrated every 3-6 months, are part of the usual speech and language intervention for children aged up to 3 years undergoing team care. Based on each child’s evaluation, early counseling is provided to parents in person or remotely. Parents are expected to apply the recommendations provided until the next visit. The EMT+PE will not be administered to participants in the control group throughout the experimental intervention period.

### Procedure

#### Therapist Training

We will recruit 3 eligible SLPs based on the study inclusion criteria. The process of implementing the protocol will be explained to them by the first author; if they are responsible for implementing it, they will participate in training sessions. They will receive training regarding the study methodology, participants, EMT+PE intervention, strategies, and fidelity of implementation for therapists and parents. SLPs will receive at least 3 in-person training sessions in accordance with the TMCR instructional model. For the Teach component, the research team will introduce speech and language strategies and their rationale. For the Model component, video examples related to the implementation of strategies by professional therapists in interacting with a child with a language disorder will be shown [12]. In the Coach component, therapists will implement strategies through role-playing. Thereafter, for the Review component, all training sessions will be monitored by researchers and therapists, and questions related to session content will be discussed and answered. For the competency-based assessment according to telehealth fidelity scales, each therapist will train a parent of a child with CP/L on the telegram platform so that the groups will consist of a therapist, a parent, and the main researcher. Then, the therapist will train the parent in at least 1 language strategy during offline and web-based sessions, and the parent will send a video of using the trained strategy when interacting with her child. Two independent experts will observe the skills-based assessment sessions and rate the therapists’ performance using telehealth fidelity scales.

#### Parent Training

Parents will receive training on specific strategies and apply them while interacting with their children at home. The competency-based assessment of parents will be defined using fidelity scales that are based on the trained strategies. The therapist will connect with parents twice a week for 3 months during the intervention course. The training sessions will be held in both offline and web-based modes. The therapist will share the material with the parents during offline sessions to teach them the strategies. For the model component, the therapist will send video examples of the strategies to the parents. Parents will be provided sufficient time to study the documents and view the video examples of the strategies. At the next stage of the administration process, the therapist will schedule a video call with the parents and they will discuss the content of the documents and video examples that would be sent, and talk about how to apply the strategies when interacting with their child. After the discussion, the parents will submit a video that shows them implementing the taught strategy. The therapist will review the videos sent. Next, the weaknesses and strengths of the video will be described on the basis of a fidelity checklist through a video call. Trainees will learn 7 supportive speech and language strategies that are arranged hierarchically from easy to difficult, including environment arrangement, match turns, modeling, prompting, time delay, expansion, and recasting [12,22]. The environment arrangement strategy aims to enhance the child’s engagement with the physical setup by selecting, arranging, and managing materials. In the matched turns strategy, parents are encouraged to match their turns of conversation with those of their child and carry out language mapping, in which parents are encouraged to mirror their child’s actions during play and incorporate language into the shared actions. Modeling involves a verbal model by the parent in which the child is encouraged to imitate. In the prompting strategy, the parent encourages the child to use an utterance at the target level in a conversational interaction. In the time delay strategy, parents encourage their child to promote initiation by providing nonverbal cues rather than relying on verbal models and commands; this includes assistance, pause in routine action (when the parent is interacting with their child), visual selection, and inadequate portion (ie, parents must ensure that the toys or equipment that they provide to their children are complete and ready to use; for example, if a doll is in a box, the child may require assistance in unboxing it and starting to play with it). In the expansion strategy, the parents repeat their child’s utterance and add a word or phrase to complete its utterance. Speech recasting involves repeating a child’s phrases with modified grammar or speech production (or both).

#### Rater Training

The child’s speech and language samples are transcribed by 4 experienced and trained raters who are blinded to the child’s group allocation (intervention or control). Before transcribing the samples, they will be provided instructions on how to rate the samples. To assess the reliability of the data, 25% of each rater’s samples will be scored by an independent expert. In case of inadequate agreement (ie, <85%) differences will be identified, and the samples will be reevaluated.

### Fidelity Assessment

#### Fidelity of Implementation for Therapists

Therapist fidelity will be assessed using an observational checklist with Likert scales. This checklist is designed in accordance with the components of the TMCR instructional model and the telepractice environment (Kaiser Telehealth Fidelity Scale). The checklist includes 5 sections: teach, model, coach, review, and overall interaction. Each section has several statements to measure implementation quality by the therapist. After training sessions with the therapists and before starting the intervention, they will be assessed using the fidelity checklist while delivering the intervention to a parent. The reliability of each therapist will be assessed (Multimedia Appendix 1).

#### Fidelity of Implementation for Parents

Parents’ ability to implement the trained EMT+PE strategies with procedural fidelity will be determined through formative visual analysis based on established learning criteria. To ensure fidelity, therapists and an independent expert will assess parents’ use of each strategy during 8 monthly sessions, using a checklist. The criteria for the strategies are as follows: environment arrangement (80%), language mapping (75%), match turns (75%), expansions (50%), modeling (40%), child’s target level (50%), prompt (80%), delay (80%), and speech recast (40%). The reliability of parents’ fidelity will be measured during the intervention [12,13] (Multimedia Appendix 2).

### Data Collection

In total, 32 children with CP/L in different provinces of Iran (Isfahan, Tehran, and Shiraz) who meet the primary inclusion criteria will be recruited. Next, the first author will call the parents and explain the process and the study’s terms of acceptance. Then, she will schedule a web-based session to complete the assessment. Parents will complete demographic information forms followed by the Age and Stages Questionnaire for their children’s developmental screening. Parents will collect speech and language samples before and after the intervention for their child in the naturalistic environment (Multimedia Appendix 3).

### Primary Outcomes

#### Speech Outcome Measures

The early phonological development of Persian-speaking monolingual children with CP/L is assessed using the Persian adaptation of the PEEPS assessment, which focuses on early acquired vocabulary [31]. The PEEPS assessment consists of 60 words that are expected to be expressed by Persian-speaking monolingual children aged 18-36 months. When administering the PEEPS assessment, an assessor first presents a picture or toy to the child as a target word; at this stage, the child is expected to respond independently. If the child does not respond, the assessor asks a question that requires the child to cue a specific word (eg, “What is this?”). If the child fails to respond again, the assessor utters a sentence that the child must complete with the target word (eg, “The baby has...”). Finally, if the child cannot produce the target word despite these cues, the assessor provides a direct command (eg, “Say...”). If the child still cannot produce the target word in response to the final command, it is marked as having provided no response.

In this study, the PEEPS assessment will be administered to assess consonant inventory based on the word-initial and word-final consonants. Also, the accuracy of speech production will be assessed by determining the total PCC, PCC stops, whole structure match, and whole-word accuracy match by an expert during a web-based session [32,33]. The evaluation session will be recorded. If the child does not participate actively in the web-based PEEPS assessment session, the parent will follow the assessor’s instructions to record their child’s responses to the speech sample and send them to the assessor.

The second version of MCDI provides parents with a categorized vocabulary list and asks them to indicate whether their children can express each word or phrase. The scale has 2 sections and assesses 680 expressive vocabulary items in 22 semantic categories among young children aged 16-30 months [34].

#### Language Outcome Measures

During the assessment, parents will engage in play sessions with their children using various toys. A 15-minute language sample will be collected remotely to determine the child’s number of different words, number of total words, and language complexity measured by mean length utterances. The assessment session will be video recorded. If the child does not engage during the web-based assessment session to collect language samples, the parent will follow the assessor’s instructions for recording the child’s responses and send the video recording to the assessor.

### Secondary Outcomes

Speech intelligibility will be measured using the Intelligibility in Context Scale, which is a parent-reported social validity tool [35]. The intelligibility rating is determined by the average response on a 5-point rating scale over 7 questions [36].

>Parents will be required to complete a postintervention satisfaction survey. The questionnaire aims to measure parent satisfaction with the telepractice EMT+PE intervention and parent training sessions (Multimedia Appendix 3).

### Statistical Analysis

#### Analysis

The analysis will be carried out using descriptive and analytical statistics. Descriptive statistics appropriate for summarizing demographic information and assessment data will be used. Preintervention differences between groups will also be estimated. The data analysis will be carried out using the SPSS (version 19; IBM Corp). The study’s outcomes will be presented as an estimation of the difference between groups, with a 95% CI and its associated *P* value. The statistical significance level will be set at α=.05*.* We will use analysis of covariance, an efficient statistical test that provides impartial estimations of an intervention’s effects, assuming random treatment assignment; this test is more powerful than other alternative statistical strategies. We will also carry out a paired samples *t* test, which compares the means of 2 variables within a single group; it estimates the differences between the values of 2 variables for each case and tests whether their average is significantly different from 0. Additionally, data from all randomized participants will be included in the intention-to-treat analysis.

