**Methods:**

A randomized controlled trial (RCT) will assess the efficacy of telepractice and the parent-implemented EMT+PE intervention in enhancing speech and language measures in toddlers with CP/L. Eligible participants will be randomly assigned to one of 2 groups: the conventional intervention group and the EMT+PE intervention group. Participants’ speech and language measures will be evaluated remotely by trained raters before and after the intervention and 2 months after the intervention. Parents of participants in the intervention group will receive 3 months of training in speech and language supportive strategies from trained therapists using telehealth fidelity scales. Parents of participants in the control group will receive the conventional speech and language intervention by cleft team therapists. Study outcomes will include language variables (mean length of utterance) and speech production variables (percent correct consonants).

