#### Intended Sample Size

Based on comparable studies with a 95% confidence level, 80% power of the test, variance of 0.0036 units, and an accuracy (improvement) of 0.06 units in the PCC, each group requires a maximum sample size of 16 participants.

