## Discussion

This study is the first RCT with follow-up, which aims to develop a protocol to evaluate the effect of parent-based EMT+PE through telepractice in Persian-speaking toddlers with nonsyndromic cleft palate.

In this study, the impact of the interventions will be evaluated by language and speech outcomes as primary outcome measures. Language outcomes include a vocabulary inventory, collected using the MCDI, mean length utterances, number of total words, and number of different words, collected through language samples and during the parent-child interaction. Speech outcomes including PCC, consonant inventory, whole-word accuracy match, and whole structure match will be collected during the PEEPS assessment. The effect of interventions will be examined for 12 weeks, with an additional 8-week follow-up period for the EMT+PE group to exclude any temporary effects that may have limited clinical value. Our results will provide information about the efficacy of the parent-implemented EMT+PE telepractice intervention in enhancing speech skills while also promoting speech production and language measures and its stability over a prolonged period. In addition, we will obtain parents’ satisfaction and score on the Intelligibility in Context Scale before and after delivering interventions as secondary outcome measures. Improvement of speech intelligibility is a long-term target of most speech therapy interventions.

The study’s limitations include its small sample size for each age group. To address the effects of such interventions, a larger-scale clinical trial is necessary. Additionally, the intervention and follow-up periods are limited in demonstrating effects. It is important to note that toddlers are in different age ranges and may require more time to develop their language and speech skills.

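### Nine measures are listed as primary and share one .05 level with no ranking or adjustment stated, while the sample size covers only PCC

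*Protocol article*

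**What the plan says.** All places are in the protocol article.

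- **Speech Outcome Measures** (under Primary Outcomes) covers consonant inventory, then accuracy assessed by "determining the total PCC, PCC stops, whole structure match, and whole-word accuracy match by an expert during a web-based session", and the MCDI expressive vocabulary list. That is six measures.
- **Language Outcome Measures** (also under Primary Outcomes) adds "number of different words, number of total words, and language complexity measured by mean length utterances". That makes nine.
- **Discussion** states that "the impact of the interventions will be evaluated by language and speech outcomes as primary outcome measures" and then lists eight of the nine; PCC for stops is not named.
- **Abstract, Methods** is shorter: "Study outcomes will include language variables (mean length of utterance) and speech production variables (percent correct consonants". It names two measures and ranks neither.
- **Analysis** says "The study’s outcomes will be presented as an estimation of the difference between groups, with a 95% CI" and a P value, and "The statistical significance level will be set at α=.05". It does not distinguish primary from other outcomes.
- **Intended Sample Size** is built on one measure: "an accuracy (improvement) of 0.06 units in the PCC", with variance 0.0036 and 80% power, giving 16 per group.

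**The concern.** A separate Secondary Outcomes section follows, holding intelligibility and parent satisfaction, so the nine measures are set apart as primary. Within the nine nothing is ordered. The article does not say whether the trial's conclusion rests on all of them, on any one, or on the one that was powered, and its own count moves from nine to eight to two to one.

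With nine co-equal primaries and one level, the 5% error rate holds for each test but not for a conclusion that may draw on any of them. If an adjustment were added later across all nine, the error rate would be controlled, but the power stated for PCC would no longer apply at the adjusted level. The choice is pressing because the Results section reports that assessments have been conducted and analysis is ongoing. An unranked list at that stage leaves the choice of main result open to the data.

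**Working it through.** **1. Reproduce the sample size.** Inputs from Intended Sample Size: difference 0.06 in PCC; variance 0.0036, so SD = √0.0036 = 0.06; "Based on comparable studies with a 95% confidence level", read as two-sided .05; power 80%. The standardised difference is 0.06 / 0.06 = 1.

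n per group = 2 × (1.960 + 0.842)² / 1² = 15.7, rounded up to 16.

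This matches the article. A one-sided calculation gives 13, so the two-sided reading is the one that fits. At 16 per group the normal approximation gives 80.7% power; the exact two-sample t calculation (noncentral t, 30 degrees of freedom) gives 78.1%.

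**2. Count the primaries.** Consonant inventory, total PCC, PCC stops, whole structure match, whole-word accuracy match and MCDI vocabulary make 6. Number of different words, number of total words and mean length of utterance make 3. The total is 9.

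**3. Chance of at least one false positive.** Assume no effect on any outcome and each tested two-sided at .05. Under independence:

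- nine outcomes: 1 − 0.95⁹ = 37.0%
- eight (Discussion): 1 − 0.95⁸ = 33.7%
- two (Abstract): 1 − 0.95² = 9.8%

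The article gives no correlation between outcomes, so a range is assumed. Simulating nine normal test statistics with a common correlation (400,000 runs) gives:

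| Assumed correlation | Any false positive, either direction | Any favouring EMT+PE |
|---|---|---|
| 0 | 37.0% | 20.5% |
| 0.3 | 32.6% | 16.5% |
| 0.5 | 27.0% | 13.5% |
| 0.7 | 20.3% | 10.1% |
| 0.8 | 16.4% | 8.2% |
| 0.9 | 12.4% | 6.3% |

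The nominal rates are 5% and 2.5%. Letting correlation be higher within speech and within language than between them gives similar values: 27.6% at 0.6 within and 0.3 between, 21.4% at 0.8 and 0.4, 16.9% at 0.9 and 0.5.

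**4. What control would cost in power for PCC.** With 16 per group and standardised difference 1, the unadjusted t test gives:

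- .05 (single primary): 78.1%
- .05 / 2 = .025 (first Holm step, two primaries): 68.0%
- .05 / 9 = .0056 (Bonferroni over nine): 45.0%

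The planned test is analysis of covariance. If 0.0036 is the unadjusted variance and the baseline-outcome correlation is 0.5 (both assumptions), the effective standardised difference is 1 / √(1 − 0.5²) = 1.155. With 29 degrees of freedom, power is then about 88%, 81% and 61% at the three levels. At a correlation of 0.7 it is about 97%, 94% and 82%.

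**The case against.** The strongest reply is that the Analysis section never says each outcome is tested without adjustment. Methods for multiplicity are commonly left to a statistical analysis plan, and none is shown here. That is fair as to the method of adjustment. It does not reach the choice of primary outcomes, the significance level and the outcome that sets the sample size: the article states all three, and they do not fit together.

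Several stronger readings are tempting and are not supported:

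- **That the error rate is at least 20%.** That floor needs a common correlation of about 0.7, which the article does not give. Higher values are plausible for some pairs: PCC for stops is part of total PCC, and the two word counts come from the same 15-minute sample. At 0.9 the rate is 12%.
- **That these are rates of a false claim for EMT+PE.** They count differences in either direction. The favourable-only rates are about half.
- **That the trial will declare success on any one significant measure.** The article states no such rule. It leaves the matter open.
- **That the paired t tests and the follow-up assessment raise the rate further.** Paired tests are within-group. The Discussion gives the 8-week follow-up to the EMT+PE group, and Usual-Care Intervention describes control assessments only before and after the intervention. The Abstract is less specific, but the article does not establish a between-group follow-up test.
- **That adjusting over all nine must be ruinous for power.** The fall to 45% is for an unadjusted t test. Analysis of covariance could soften it considerably.

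It is also fair to object that PCC as sole primary would drop the language half of the stated primary objective. The option with one primary in each domain therefore stands on equal terms.

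**Conclusion.** The point holds at protocol level. The primary outcome is not fixed, one unranked level of .05 covers nine measures, and only PCC was powered. If nothing is affected and all nine are tested two-sided at .05, the chance of at least one false positive lies between about 12% and 37% for common correlations from 0.9 down to 0, and between about 6% and 20% counting only results that favour EMT+PE. Independence gives the top of each range; the rest depends on assumed correlations. Every scenario examined exceeds the nominal rate at least twofold. The sample size itself reproduces and is not in question here.

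**What to change.** Rank the outcomes before results by arm are seen, in a dated and disclosed change. Two options are sound:

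- **One primary.** Total PCC at the end of the 3-month intervention, tested two-sided at .05. This is the outcome the sample size used, so 16 per group and the stated power stand and the error rate is 5%. The cost is that every language measure becomes secondary, although the primary objective names both domains.
- **Two primaries.** PCC and mean length of utterance, with Holm adjustment. This keeps both domains and matches the pair in the Abstract. The cost is power: about 68% for PCC at the first Holm step by an unadjusted t test (against 78% at .05), or about 81% under analysis of covariance on the assumptions in the working. The article gives no variance or target difference for mean length of utterance, so its power cannot be stated.

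Under either option, make the remaining measures secondary. Report them as estimates with 95% CIs and no confirmatory claim, or with Holm-adjusted P values. Bring the Abstract, Primary Outcomes, Analysis and Discussion to the same list.

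No new data or participants are needed, but there will be fewer headline P values. Because follow-up has ended, the change is more than wording: it needs a date and a statement of what had been seen. If analysis by arm has already begun, say so and label the ranking as post hoc.

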**Objective:**

This study aims to determine and compare the effectiveness of telepractice and the parent-implemented EMT+PE intervention on language and speech measures in toddlers with CP/L with usual interventions and determine the effectiveness maintenance of the intervention.

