### Aims

#### Primary Objectives

Our primary objective is to determine the effectiveness of a parent-based telepractice EMT+PE intervention on language and speech outcomes in toddlers with CP/L.

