#### Secondary Objectives

Our secondary objectives are to compare the effectiveness of this parent-based telepractice EMT+PE intervention with usual-care interventions and determine the effectiveness of the intervention in the follow-up period.

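### The primary objective names no comparator, the randomised comparison with usual care is ranked second, and a within-group paired t test is added with no stated role

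*Protocol article*

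**What the plan says.** **Objectives.** Under Primary Objectives: "Our primary objective is to determine the effectiveness of a parent-based telepractice EMT+PE intervention on language and speech outcomes in toddlers with CP/L". No comparator is named. Under Secondary Objectives: "Our secondary objectives are to compare the effectiveness of this parent-based telepractice EMT+PE intervention with usual-care interventions", together with effectiveness in the follow-up period. The Abstract's Objective makes no such split: "This study aims to determine and compare the effectiveness of telepractice and the parent-implemented EMT+PE intervention", with usual interventions as the comparator.

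**Analysis.** The Analysis section states that "outcomes will be presented as an estimation of the difference between groups", with a 95% CI and P value. It then says "We will use analysis of covariance, an efficient statistical test", and justifies this by random assignment. After that it adds a paired samples t test, described as one "which compares the means of 2 variables within a single group", which tests whether the average change differs from 0. The section assigns no test to any objective. On alpha: "The statistical significance level will be set at α=.05".

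**Sample size.** Intended Sample Size gives a 95% confidence level, "80% power of the test", a variance of 0.0036, an improvement of 0.06 in PCC, and 16 per group.

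**Setting.** Children are 18 to 36 months old at entry and the intervention lasts 3 months. The Discussion describes the 8-week follow-up for the EMT+PE group only.

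**The concern.** In a randomised trial, effectiveness is the difference between arms. Here that difference is a separate, lower-ranked objective, so it is unclear what would satisfy the primary one. Either the two objectives are the same question listed at two ranks, or the primary one can be answered without the control arm. The text needs correcting in both cases.

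The second possibility matters because the plan contains a test that would fit it. Over 3 months, a child of 18 to 36 months is expected to gain speech and language without EMT+PE. The Discussion itself recognises that toddlers are still developing these skills. A pre-post change in one arm also includes familiarity with the assessment and any regression to the mean. A paired t test against zero counts all of this together with any treatment effect. Only the comparison with the concurrent control arm removes it.

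At stake is the trial's main conclusion. A significant change in the EMT+PE arm could be reported as meeting the primary objective when children under usual care improved just as much.

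**Working it through.** **1. Which comparison was the trial sized for?**

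Inputs from Intended Sample Size: variance 0.0036, so SD = √0.0036 = 0.06; difference 0.06; power 80% (z = 0.8416). Alpha is 0.05. Its sidedness is not stated, so two-sided is assumed (z = 1.96).

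- Two-sample comparison: n per arm = 2 × (1.96 + 0.8416)² × 0.0036 / 0.06² = 2 × 7.849 = 15.70, rounded up to **16**. This is the plan's figure.
- The same with one-sided alpha 0.05: 13 per arm. No match.
- Single group, pre-post, taking 0.06 as the SD of change: n = (1.96 + 0.8416)² × 0.0036 / 0.06² = 7.85, rounded up to 8, or 10 by the exact t test. No match.

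So 16 per group fits a two-sided comparison of two arms, which is the comparison that the objectives rank second. At 16 per arm the power is 80.7% by the normal approximation and 78.1% by the exact two-sample t test.

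**2. What can the paired t test show when treatment does nothing?**

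From the protocol: n = 16 in the EMT+PE arm, SD 0.06, two-sided 5% test (critical t on 15 df = 2.131).

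Assumed, because the article gives neither: growth g over 3 months, the same in both arms, of 0.02 or 0.03 in PCC (one third and one half of the planned 0.06); pre-post correlation r of 0.5, 0.7 or 0.8. There is no treatment effect.

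SD of change = 0.06 × √(2(1 − r)). Noncentrality = g × √16 / SD of change. The probability of a significant result comes from the noncentral t distribution.

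| r | SD of change | g = 0.02: noncentrality, P(significant) | g = 0.03: noncentrality, P(significant) |
|---|---|---|---|
| 0.5 | 0.0600 | 1.33, 24% | 2.00, 46% |
| 0.7 | 0.0465 | 1.72, 36% | 2.58, 68% |
| 0.8 | 0.0379 | 2.11, 51% | 3.16, 84% |

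**3. What does the planned ANCOVA do in the same situation?**

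Simulation with 16 per arm, equal growth in both arms, no treatment effect and 10,000 runs per setting (r = 0.3, 0.5, 0.7; g = 0.03, 0.06): the baseline-adjusted ANCOVA was significant in 4.8% to 5.3% of trials. Growth common to both arms goes into the intercept and cancels from the group contrast, so this does not depend on the size of g.

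**The case against.** The strongest reply is that the plan already contains the right analysis. ANCOVA is named first and tied to random assignment, outcomes are to be presented as between-group differences with CIs, and the paired test comes afterwards as an addition. The Abstract joins determining and comparing in one aim, and the Background ends on a comparison with usual care. The sample size points to a two-arm contrast. On this view the two objectives are loosely worded rather than a decision to demote the randomised comparison. All of that stands, and it limits the point to the hierarchy and the unassigned test.

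A reader might infer more: that the primary objective is defined as within-arm change and that the paired t tests are its analysis. The article does not say so. It never calls the primary objective within-arm or pre-post, and it links the paired test to no objective. Nor does it plan to contrast significance in one arm with non-significance in the other.

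The percentages can also be over-read. The paired test's null hypothesis is no change. With real growth that null is false, so 24% to 84% is the test's power to detect growth. It becomes a false-positive rate for treatment only if the change is reported as a treatment effect.

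Finally, removing every within-arm analysis would go too far. If follow-up data exist for the EMT+PE arm alone, a within-arm summary is a natural description of maintenance.

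The reply does not remove the ambiguity. The article still ranks an objective without a comparator above the comparison, and still gives a significance test within one group no stated limit on its use.

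**Conclusion.** The concern holds in this form: the stated order of objectives does not match the trial's randomised design, its main analysis or its sample size, and a within-group significance test has no defined role. The documents do not support saying that the trial rests on paired tests.

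The mismatch itself rests only on the article's text and the reproduced 16 per group, with two-sided alpha as the one assumption. The illustration rests on assumed growth and correlation: with no treatment effect, the paired test would be significant in about 24% to 84% of trials, against about 5% for the ANCOVA. Other assumptions would change the percentages. For any positive shared growth, the paired test is significant more often than its nominal 5% with no treatment effect at all.

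The correction is worth making because it settles which result decides the conclusion of a 32-child trial. The Results section says analysis was still ongoing at publication.

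**What to change.** 1. Restate the primary objective as the difference between EMT+PE and usual care at the end of the 3-month intervention, estimated by the baseline-adjusted ANCOVA with its 95% CI. Make this the sole basis for any effectiveness claim, and merge the present secondary comparison into it.
2. In the Analysis section, state that within-arm changes, including maintenance in the EMT+PE arm at follow-up, are descriptive: means with CIs and no inference about effectiveness.
3. Disclose the change and its date. The Results section says therapy and follow-up ended in June 2023 and that pre- and postintervention assessments had been done, so it comes after data collection and should be reported as such.

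The cost is rewording in Primary Objectives, Secondary Objectives and Analysis, plus the disclosure. No new data are needed, and the sample size stays at 16 per arm because it already follows from the two-sample formula.
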